### Randomization and consent

If the eligibility criteria are met, the patient has signed the information and consent form and the date for the surgery has been set, the participants will be randomized into the intervention or control group (usual care group). The random allocation sequence is performed computer-aided using a professional online tool for randomized clinical trials called “Randomizer” (https://www.randomizer.at/, Randomizer Version 2.1.0, Institute for Medical Informatics, Statistics and Documentation, Medical University of Graz). To ensure a balanced allocation sequence, a stratified permuted block randomization with stratification by gender (female or male) and type of care (knee or hip) will be used. We do not stratify by age, as only geriatric patients are included into the trial (age ≥ 70). The block sizes will not be disclosed, to ensure concealment. Thus, randomization will be conducted without any influence of the principal investigators, physicians, therapists, statisticians, or the research assistant.

### The interventions

#### The SOG care model group (experimental group)

The intervention and outcome assessments are summarized in Fig. 2.

**Fig. 2 Fig2:**
[figure not shown]
Study intervention and outcome assessments

### Screening

First, a screening is carried out to identify geriatric patients at increased risk of adverse health outcomes. For this purpose, the Identification of Seniors at Risk (ISAR) screening tool [25], which is used in hospital emergency departments, and a screening tool we developed specifically for elective orthopaedic surgery patients, the SOG screening tool, are used. Screening for malnutrition is performed by Nutritional Risk Screening (NRS) [26]. There is also a consultation with a geriatrician with physical examination and review of polypharmacy and comorbidities. The screening is completed by a SOG laboratory blood test.

### Appropriate preoperative intervention (API)

After reviewing the screening and assessment results, an appropriate preoperative intervention (API) is carried out. The API is aimed at the patient himself/herself, the general practitioner and, if applicable, the treating specialists. Contact with the participant and the external doctors can be made by telephone and/or in writing via doctor’s report/information material. Re-appointment to the university outpatient clinic is also possible. The API includes the Risk Factor Liaison Service (RiFLS) at the hospital. This addresses the modifiable risk factors of anaemia, malnutrition, vitamin D deficiency, obesity, diabetes mellitus and nicotine abuse. Depending on the comorbidities, physical examination findings and laboratory blood parameters, further diagnostic clarification is recommended or carried out. This also includes consultation with other specialists such as cardiologists, angiologists or neurologists. Optimization of polypharmacy with adjustment for age and comorbidities by the geriatrician, management of anticoagulation and patient blood management (PBM) is also part of the intervention before surgery.

### Preoperative/inpatient admission

A comprehensive geriatric assessment (CGA) consisting of Barthel Index [27], Instrumental Activities of Daily Living (IADL) scale [28], Social situation (Nikolaus) [29], Short Physical Performance Battery (SPPB) [30], Fried Frailty Phenotype [31], Mini Mental State Examination (MMSE) [32], Geriatric Depression Scale (GDS-15) [33] and NRS [26] is performed on admission. There is a physical examination by the orthopaedic surgeon and geriatrician and a SOG laboratory blood test. Perioperative pain management is adapted to older, multimorbid patients and does not include NSAIDs. Benzodiazepines are omitted from premedication. The patient already receives crutch training by physiotherapy before surgery.

### Perioperative/surgery

The patient is transported to the operating room and back to the ward by a nurse known to the patient. Aids such as glasses or hearing aids are given to the patient. Surgery is performed according to the fast-track surgery principle with prilocaine spinal anaesthesia or general anaesthesia and minimally invasive surgical techniques. Spinal anaesthesia is preferred. General anaesthesia is only used if the patient refuses spinal anaesthesia or it is not anaesthesiologically feasible. Redon drains and urinary catheters are not used.

### Postoperative management

After surgery, the patient remains in the recovery room for 2–3 hours for monitoring, unless complications arise or other reasons require longer monitoring. In the recovery room, early mobilisation is performed by physiotherapy and nursing. The patient is then transferred to a special orthogeriatric ward (SOG unit). The SOG unit is a specially equipped ward for elderly patients, where  special attention is paid to delirium prevention. There is also a common room for patients on the ward to eat and socialise. Postoperatively, the participant receives multimodal orthogeriatric care. This includes care by a multiprofessional orthogeriatric team on the ward, consisting of orthopaedic surgeon, geriatrician, activating-therapeutic nursing, intensified physiotherapy (twice a day), occupational therapist, psychologist, nutritional therapist and team-integrated medical social workers. There is a daily joint ward round by the orthopaedic surgeon, geriatrician and nursing. The entire orthogeriatric team meets once a week for a team meeting, where each individual patient is discussed on an interdisciplinary basis. A standardized screening for postoperative delirium is performed daily by the nursing staff using the Nursing Delirium Screening Scale (NU-DESC) [34]. Further postoperative geriatric assessment includes Barthel Index [27], SPPB [30], Fried Frailty Phenotype [31], Mini Mental State Examination (MMSE) [32], Geriatric Depression Scale (GDS-15) [33] and NRS [26]. A standardized blood laboratory test is performed on postoperative days 1, 3 and 5. Drug therapy is monitored and adjusted daily by the geriatrician. For the orthogeriatric ward, there are standards for pain management (without NSAIDs), sleep medication, antiemetics and standards for monitoring vital signs.

#### Control group

Patients in the control group receive standard care for total hip and knee arthroplasty. Pre-, peri- and postoperative care is provided according to the orthopaedic surgeon’s instructions. The standard surgical principle with the use of Redon drains and urinary catheters is performed. The patient remains in the recovery room until the following day. Mobilisation with physiotherapy takes place on the first day after surgery. Further inpatient care is provided on an orthopaedic ward. Postoperatively, physiotherapy is performed once a day. No other therapies are planned. The usual orthopaedic standards for pain management (with NSAIDs) and blood lab tests apply. Daily ward rounds are carried out by the orthopaedic surgeon and the orthopaedic nursing staff.

### Study outcomes

The study outcomes will be collected preoperative (baseline), postoperative day 1 to 7, 4 to 6 weeks and 3 months after surgery. Figure 1 summaries the primary, secondary and tertiary outcomes and measurement time.

### Primary outcome

*Short Physical Performance Battery (SPPB)* is a measure of physical functioning [30]. SPPB evaluates balance, mobility and muscle strength by examining an individual’s ability to stand in different positions, time to walk 4 m, and time to rise up from and sit down on a chair 5 times [30]. The tests are scored between 0 and 4, leaving a maximum score of 12 [30]. The SPPB is performed preoperatively on admission to hospital, on the 3rd day after surgery, on the 7th day after surgery before discharge from hospital, and at 4–6 weeks and 3 months after surgery.

### Secondary outcomes

Frailty will be assessed using *Fried Frailty Phenotype* which is composed of five items, three self-reported (unintentional weight loss, exhaustion and physical activity), and two performance-based items (strength (assessment based on the handgrip strength measurement) and speed). It is a widely used and validated frailty measure. Each item is scored 0 or 1 with a final score out of 5; higher scores indicate greater frailty [31, 35]. It is used preoperatively on admission to hospital, on the 7th day after surgery before discharge, at 4–6 weeks and 3 months after surgery.

The *Barthel Scale/Index* is an ordinal scale used to measure performance in activities of daily living (ADL). Ten variables describing ADL and mobility are scored, a higher number being a reflection of greater ability to function independently following hospital discharge [27]. It is used preoperatively on admission to the hospital, on the 7th day after surgery before discharge, at 4–6 weeks and 3 months after surgery.

The Lawton & Brody *Instrumental Activities of Daily Living Scale (IADL)* is an appropriate instrument to assess independent living skills [28]. These skills are considered more complex than the basic activities of daily living as measured by the Barthel Index. There are eight domains of function measured with the Lawton IADL scale. Participants are scored according to their highest level of functioning in that category. A summary score ranges from 0 (low function, dependent) to 8 (high function, independent) [28]. The IADL scale is performed on admission to hospital and at 4–6 weeks and 3 months after surgery.

The *Mini Mental State Examination (MMSE)* is a 30-point questionnaire that is used extensively in clinical and research settings to measure cognitive impairment. The test examines functions such as registration (repeating named prompts), attention and calculation, recall, language, ability to follow simple commands and orientation. Any score of 24 or more (out of 30) indicates a normal cognition. Below this, scores can indicate severe (≤9 points), moderate (10–18 points) or mild (19–23 points) cognitive impairment [32]. Testing is done preoperatively on admission to hospital, on the 1st postoperative day, on the 7th day after surgery before discharge, and after 4–6 weeks and after 3 months after surgery.

The 15-item *Geriatric Depression Scale (GDS-15)* is a short form of GDS and is used to screen, diagnose, and evaluate depression in elderly individuals. In scoring the GDS, 1 point is awarded for each answer that indicates depression. If a person scores more than 5 on the 15-question assessment, this may indicate the presence of depression [33]. The test is performed preoperatively on admission to hospital, on the 1st postoperative day, on the 7th day after surgery before discharge, and after 4–6 weeks and after 3 months after surgery.

The purpose of the *Nutritional Risk Screening (NRS)* system is to detect the presence of malnutrition and the risk of developing malnutrition in the hospital setting. It includes four questions as a pre-screening. If one of these is answered positively, a screening follows which includes surrogate measures of nutritional status, with static and dynamic parameters and data on the severity of the disease (stress metabolism). For each parameter, a score from 0 to 3 can result. Age over 70 years is considered as a risk factor, and is included in the screening tool as well, giving 1 point. A total score of ≥3 points means that the patient is at risk of malnutrition or already malnourished and therefore a nutritional therapy is indicated [26]. The NRS is assessed for the first time in the university outpatient clinic at the time of the screening. In addition, it is applied preoperatively on admission to hospital, on the 7th day after surgery and after 4–6 weeks and 3 months after surgery.

The *Nursing Delirium Screening Scale (Nu-DESC)* is an observational five-item scale for detecting delirium. The Nu-DESC has five dimensions with point values of 0 = non-existent, 1 = present and 2 = strongly present, the probability of delirium is given from a sum point value ≥ 2. It can thus be used as a metric scale of 0–10 with 10 = most severe delirium [34]. It is applied daily during inpatient stay.

The *Western Ontario and McMaster Universities Osteoarthritis Index (WOMAC)*, which is a pain index measurement for OA, is the most widely used parameter for knee joint function and also a tool for evaluating disorders related to OA of the lower extremities. The WOMAC consists of a total of 24 questions and three subscales. Among them, there are five questions related to pain, two questions related to stiffness, and 17 questions related to difficulties in performing activities of daily living in relation to physical function. The disease-specific tool is of use in clinical evaluation of changes in pain-related health status and clinical outcomes. The WOMAC is valid and reliable for defining function in lower extremity disorders [36, 37]. It is used preoperatively, 4–6 weeks and 3 months after surgery.

*Health and Quality of Life Questionnaire (EQ-5D-5 L)* measures the patient’s health-related quality of life. Five questions are scored on a 5-point scale. Additionally, the self-rated health is reported on a vertical, visual analogue scale [38, 39]. The measurements are taken preoperatively, 4–6 weeks and 3 months after surgery.

*PPP33* is a patient-oriented questionnaire with 33 items that allows participants to assess the quality of the perioperative period. Not only postoperative somatic disorders are addressed, but all relevant aspects of the entire perioperative period [40]. It is used on the 7th day after surgery before discharge from hospital.

Other secondary outcomes listed in Fig. 1 such as *polypharmacy*, *complications/morbidity (Clavien-Dindo classification)* [41] and *mortality* are collected in standardized forms. The time of data collection is presented in Fig. 1.

### Tertiary outcomes

The tertiary outcomes *length of hospital stay*, *reoperation rate*, *transfusion rate*, *rehospitalization rate* and *time to rehabilitation* are captured in the acute phase, during inpatient stay, and 4–6 weeks and 3 months after surgery.

### Sociodemographic - and other variables

Age, sex, adiposity (body mass index), smoking, medication list, anticoagulants, comorbidities, social situation (Nikolaus) [29], ISAR screening tool [25] and our SOG screening tool are variables captured at baseline. The SOG screening laboratory test includes C-reactive protein (CRP), complete blood count (CBC), Quick-%, international normalized ratio (INR), partial thromboplastin time (PTT), serum sodium, serum potassium, serum calcium, serum creatinine (Cr), blood urea nitrogen (BUN), creatinine clearance (Ccr), serum protein, serum albumin, total bilirubin, aspartate aminotransferase (AST), alanine aminotransferase (ALT), gamma glutamyltransferase (GGT), alkaline phosphatase, blood glucose level, glycosylated hemoglobin A (HbA1c), serum iron, ferritin, transferrin, transferrin saturation, thyroid-stimulating hormone (TSH), folate, vitamin B12, vitamin D, and at the time of hospital admission, an additional urinalysis.

### Adherence to the program

To ensure adherence to the program, the doctors, nurses and therapists involved in the project are trained and motivated. The research nurse accompanies the participants to all examinations such as laboratory tests and geriatric assessments that are required as part of the study. The doctors, nurses and therapists document the collected data directly in the electronic database GERD or in documentation sheets. This is checked by the research assistants in a protocol list. Already during the inpatient clinic stay, each participant receives the appointments for the follow-up examinations in writing.

### Adverse events

Adverse events or harm from any source will be reported to the research team and recorded on a structured form. Any serious or unexpected adverse events that occur during the study and may affect the safety of the study participants or the conduct of the study will be reported immediately in writing to the Ethics Committee.

### Data collection and management

Figure 1 provides an overview of the data collection timeline. Screening and follow-up examinations after 4–6 and 12 weeks take place in the university outpatient clinic. The preoperative assessment is carried out on the premises of the central patient admission of the orthopaedic university hospital.

All other peri−/postoperative data (day 0–7 after surgery) are collected on the wards of the orthopaedic university hospital. The study assessors received extensive training before the start of the study, in which they were individually trained on how to collect the study outcome measures in frail older people. All data will be stored at the research server at the hospital. Study data will be managed using electronic data capture tools. The study database will be password protected and kept on a secure network system. Passwords are changed at regular intervals. A complete back up of the database will be performed twice a week. A formal Data Monitoring Committee (DMC) is not required for this trial as risks are considered minimal.

### Trial management

The coordinating centre for the study is at the Department of Orthopaedic Surgery, Regensburg University Medical Center, Germany. The study coordinator and research assistants are responsible for submitting study documents, planning and conducting the study, collecting and managing data, receiving and storing consent forms, and publishing the study results. Statistical analysis will be performed by the Department of Health Economics, Technical University of Munich (TUM). The study is fully funded by the German Federal Joint Committee - GBA (Grant no. 01VSF19030 (SOG)) and the funding management is carried out by the German Aerospace Center. Research reports will be written every quarter and the appropriate use of the funding will be monitored in an annual interim report. The final results of this study are expected to be available in 2024.

### Data analysis

The evaluation is carried out as an intention-to-treat analysis. Baseline demographic and clinical characteristics of the participants will be described using summary statistics (means, standard deviations and frequencies). Significance in differences will be tested using t-test for continuous variables with normal distribution, chi-square test for categorical variables and Mann-Whitney U-test for continuous variables with non-normal distribution. Normality of the distributions will be tested graphically. We will examine the difference preoperatively and postoperatively (3 days, 7 days, 4–6 weeks, 3 months) with regard to the primary outcome variable (SPPB score) in the intervention and control group, as well as between the groups (postoperatively). To assess significance in differences we will use paired-samples t-test. Although the random assignment of the patients should provide unbiased results, the need for an adjusted analysis will be considered. To this end, in order to account for potential confounders, we will consider general linear models (e.g. multivariate linear regression and analysis of covariance [42] to evaluate between-group differences in SPPB scores. The need for an adjusted analysis within generalized linear (mixed) models will be considered as well. Secondary endpoints will be analysed both descriptively and standardized within adjusted regression analyses. *P*-values *p* < 0,05 will be considered as statistically significant. Detailed sensitivity analyses are planned for all outcomes of the intervention. Potentially missing data will be completed using adapted techniques (e.g. multiple imputation).

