### Sample size

The sample size calculation is based on the primary endpoint of the analysis - “Improvement of Mobility”, measured by Short Physical Performance Battery (SPPB). According to previous studies, the clinically relevant difference between the two groups is conservatively estimated at 0,5 points with an expected standard deviation of 1,48 points [24]. Due to a 1:1 randomization, the number of cases per group is 139 to achieve a power of 80% at a 5% significance level (Gpower). Taking into account a possible dropout rate of 10%, a total of 310 patients should to be randomized.

The patient is not informed about the result of the randomization. The allocation is only known to the team directly treating the patient. In particular, the investigators who perform the post-intervention testing are blinded. For the patients, blinding is ensured by the fact that the patients in the control group also receive physiotherapy after surgery. Furthermore, the planned length of stay in hospital is the same for both study groups. An interdisciplinary ward round is simulated, but without orthogeriatric care in the actual sense. Very rare circumstances that may lead to emergency intervention during the study, and therefore possibly emergency unblinding, may include unpredictable highly pathological, life-threatening assessment, examination or laboratory results.

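### The Data analysis section commits to no independent-groups comparison of mean SPPB, although the trial is sized on a 0.5-point mean difference

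*Protocol article*

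**What the plan says.** The Sample size section states that "the clinically relevant difference between the two groups is conservatively estimated at 0,5 points with an expected standard deviation of 1,48 points" and that "the number of cases per group is 139 to achieve a power of 80" per cent. Under Primary outcome, SPPB is the sum of three component tests: "The tests are scored between 0 and 4, leaving a maximum score of 12". It is measured on admission and then at four postoperative times: day 3, day 7, 4 to 6 weeks and 3 months.

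The Data analysis section says four things that bear on how the arms are compared:

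- Directly after the sentence on baseline summaries comes a general rule. Normal continuous variables get a t-test, categorical variables a chi-square test, and the remainder a "Mann-Whitney U-test for continuous variables with non-normal distribution. Normality of the distributions will be tested graphically".
- SPPB then has its own sentence. It is to be compared before and after surgery within each group, and between the groups postoperatively.
- The next sentence names the test for these differences: a paired-samples t-test.
- General linear models, including ANCOVA, are to be considered for between-group SPPB differences, and so are generalized linear (mixed) models.

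**The concern.** The quantity the trial is sized for is a difference between two independent means. None of the statements in Data analysis commits to estimating it. The paired test addresses change within patients and cannot compare two arms made up of different people. The linear models are optional. What remains as a firm rule for independent samples is the choice between t-test and Mann-Whitney, made by looking at the data.

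That choice changes the hypothesis. A t-test concerns the difference in means. Mann-Whitney concerns the probability that a patient in one arm scores higher than a patient in the other, and gives no estimate to set against 0.5 points. A Hodges-Lehmann shift, which the article does not mention, would match the mean difference only under a pure shift.

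SPPB is a bounded whole-number score, so its plots may look acceptable at one visit and not at another. The primary outcome could then be reported on different scales over time, with the choice made after the outcome data were seen.

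**Working it through.** **1. Inputs.** From Sample size: difference 0.5, SD 1.48, power 80%, 5% level, 1:1 allocation, 10% dropout. Sidedness is not stated.

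**2. Reproducing the plan's figure.**
- d = 0.5 / 1.48 = 0.338.
- Normal approximation, two-sided, two samples: n = 2 × (1.960 + 0.842)² / 0.338² = 2 × 7.849 / 0.1141 = 137.5, so 138 per group.
- Exact noncentral t: power 0.7986 at 138 and 0.8014 at 139, so 139 per group.
- Dropout: 139 / 0.9 = 154.4, so 155 per group and 310 in total.
- Alternatives do not fit. A one-sided two-sample test gives 109 per group. A paired test, taking 1.48 as the SD of differences, gives 7.849 / 0.1141 = 68.8, about 69.

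The figure is therefore a two-sided two-sample t-test on means.

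**3. What that comparison would deliver.** Standard error of the difference = 1.48 × √(2/139) = 0.178, so the 95% CI half-width is 1.97 × 0.178 = 0.35 points. This interval can be read directly against 0.5. At 139 per arm, a mean of a score limited to 0–12 is close enough to normal for a Welch t-test or linear model to be valid without normal data, so the switch is not needed for validity.

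**4. Power if Mann-Whitney is used instead, pure shift of 0.5.** Replace n by n × ARE (asymptotic relative efficiency against the t-test).

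| Shape | ARE | Power at 139 per group | n per group for 80% |
|---|---|---|---|
| t-test benchmark | 1 | 0.801 | 139 |
| Normal | 3/π = 0.955 | 0.783 | 146 |
| Least favourable shape | 0.864 | 0.741 | 161 |
| Laplace | 1.5 | 0.931 | 93 |

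**5. Check on 0–12 whole-number scores.** A latent normal was rounded and clipped to the scale, with control SD 1.48 and a mean difference of 0.5 (20,000 simulated trials per case, tie-corrected Mann-Whitney).
- Control means 3 to 9: Mann-Whitney 0.78–0.80, t-test 0.80–0.81.
- Control means 10 to 11, where there is a ceiling: Mann-Whitney 0.82–0.92, t-test 0.82–0.90.
- Right-skewed (exponential) shift: Mann-Whitney 0.96, t-test 0.79.

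At the trial's own parameters the rank test costs at most about 2 points, and it sometimes gains.

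**6. Where a large loss would come from.** Assume most patients score about 9 and the whole mean gain comes from fewer patients in a low-scoring subgroup.

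| Control subgroup | Mean gain | Mann-Whitney | t-test | Control SD |
|---|---|---|---|---|
| 10% at about 4 | 0.50 | 0.32 | 0.81 | 1.83 |
| 12% at about 5 | 0.48 | 0.43 | 0.84 | 1.66 |
| 20% at about 6 | 0.50 | 0.66 | 0.85 | 1.59 |
| 30% at about 6.5 | 0.50 | 0.76 | 0.83 | 1.55 |

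These shapes are assumptions. In each, the control SD exceeds the planned 1.48, and the article gives no SPPB distribution that would support them.

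**The case against.** The strongest case against the point is that the general rule follows the sentence on baseline characteristics and may be meant only for those variables. SPPB has its own sentences, and the methods named there (paired t-test, linear regression, ANCOVA) all concern means. Choosing a test by distribution is a conventional summary line, the article is condensed, and an analysis plan may give the detail.

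Much of this stands, and it rules out two stronger readings. A reader might infer that Mann-Whitney is the test most likely to be used on SPPB. No sentence assigns it to SPPB, so the text does not support that. Nor can the inference be spread to the main outcomes at large, since secondary endpoints are promised adjusted regression. A reader might also infer that much of the stated power would be lost. Steps 4 and 5 show otherwise for a shift. The losses in step 6 need an effect confined to a low-scoring minority, whereas the hypothesis in the article is improved mobility in general.

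The objection does not rescue the SPPB comparison. If the general rule covers SPPB, the test depends on a plot. If it covers baseline variables only, the one test firmly named for SPPB is the paired t-test, which cannot compare the arms. Both faults lie in what the article states, so leaving detail to an analysis plan does not answer them.

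**Conclusion.** The point holds in this form: the article sizes the trial on a two-sample difference in mean SPPB but does not commit to an analysis that estimates it. The paired test named for SPPB is wrong for the between-group comparison, the mean-based models are optional, and the general rule, if it applies, lets a plot choose the hypothesis visit by visit.

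The power consequence is minor. If Mann-Whitney were used under a shift, expect about 78% instead of 80%, and at worst about 74%; skewed or heavy-tailed shapes can raise it above the t-test. These figures rest on the article's 0.5 and 1.48, a two-sided 5% level and a pure shift. What is at stake is whether the primary result is one prespecified estimate that can be read against 0.5 points.

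The conclusion is limited to SPPB. Whether length of stay and time to rehabilitation should also be compared by means is a trade-off on which reasonable statisticians differ.

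**What to change.** For SPPB, remove the graphical normality switch and state that the between-group difference at each postoperative time is estimated as a difference in means with 95% CI, whatever the distribution looks like. A Welch t-test would do. A linear model or ANCOVA on baseline SPPB with robust standard errors is better, and should be committed to rather than considered. Limit the paired t-test to change within a group. Keep Mann-Whitney as a labelled sensitivity analysis.

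This costs a sentence or two, with no extra data or patients and no change to the sample size. The small downside is that with marked skew or outliers a comparison of means can be somewhat less powerful than a rank test.

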The objectives of the randomized controlled trial are.The primary objective is to examine the impact of comprehensive geriatric assessment, appropriate preoperative intervention, fast-track surgery principle and multimodal perioperative care on a SOG unit (SOG care model) versus standard care after total hip and knee arthroplasty on mobility on postoperative day 3 and 7, 4 to 6 weeks and 3 months after surgery.The secondary objectives are to explore potential efficacy of the comprehensive geriatric assessment, appropriate preoperative intervention, fast-track surgery principle and multimodal perioperative care on a SOG unit (SOG care model) versus usual orthopaedic care after total hip and knee arthroplasty on overall health, disability, morbidity, mortality, postoperative complications including delirium, cognition, mood, frailty, activities of daily living/instrumental activities of daily living, malnutrition, pain, polypharmacy, PROM and PREM on postoperative day 1 to 7, 4 to 6 weeks and 3 months after surgery.The tertiary objectives are to test the effect of comprehensive geriatric assessment, appropriate preoperative intervention, fast-track surgery principle and multimodal perioperative care on a SOG unit (SOG care model) versus standard care after total hip and knee arthroplasty on length of hospital stay, readmission rate, reoperation rate, transfusion rate and time to rehabilitation.

In addition, within the framework of the study, we aim:4.To develop and validate a new screening tool (SOG screening) for geriatric patients undergoing elective orthopaedic surgery.5.To develop and validate a routine preoperative laboratory test for orthogeriatric patients.

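### SPPB is primary at four unranked postoperative times with no success rule, while the sample size covers one comparison with no time attached

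*Protocol article*

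**What the plan says.** Three sections of the protocol article attach the primary outcome to the same four postoperative times.

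- **Objectives and research hypothesis:** the primary objective is the effect of the care model "on mobility on postoperative day 3 and 7, 4 to 6 weeks and 3 months after surgery".
- **Primary outcome:** SPPB is measured at admission and then at day 3, day 7, 4–6 weeks and 3 months. No assessment is singled out.
- **Data analysis:** SPPB is examined before surgery and "postoperatively (3 days, 7 days, 4–6 weeks, 3 months) with regard to the primary outcome variable (SPPB score"), within each arm and also between the arms postoperatively. P-values below 0.05 "will be considered as statistically significant". Linear and mixed models are mentioned, but only as something to be considered.

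The **Sample size** section rests on one primary endpoint. The difference is "conservatively estimated at 0,5 points with an expected standard deviation of 1,48 points", and "the number of cases per group is 139 to achieve a power of 80% at a 5% significance level". No time point is given for that difference or that standard deviation. After an allowance of 10% for dropout, 310 patients are to be randomized.

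The article states no order among the four times, no requirement that all succeed, no adjustment and no single overall contrast.

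**The concern.** The trial is sized for one test, but its primary objective has four parts of equal standing. A 5% level and 80% power describe one decision. With four comparisons, what they mean depends on how the four results are combined into a verdict on the primary hypothesis, and the article does not say.

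The Discussion states that a successful trial may lead German health insurers to cover the care model. It also cites, as a merit of SPPB, that it detected a difference within days of surgery in another study. A result that is significant early and not at 3 months, or the reverse, is therefore a realistic outcome. The article gives no basis for saying whether that trial met its primary objective, and a choice made after the data are seen would decide the answer.

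**Working it through.** **Inputs.** From Sample size: difference 0.5, SD 1.48, power 80%, level 5%, 1:1 allocation, dropout 10%. From the primary objective, Primary outcome and Data analysis: four postoperative times, p < 0.05. The correlation between the test statistics at different times is not given, so it is an assumption and is varied below.

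**Step 1: reproduce the stated sample size.** Normal approximation, two-sided 5%:

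n per group = 2 × (1.960 + 0.842)² × 1.48² / 0.5² = 137.5, rounded up to 138.

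The exact noncentral-t calculation gives 139 (power 0.801; 138 gives 0.799). A one-sided 5% test would need only 109 (normal approximation), so the figure is one two-sided comparison. Dropout: 139 / 0.9 = 154.4, rounded up to 155 per group, or 310 in total. The plan's arithmetic is right.

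**Step 2: four tests, success if any one is significant.** If independent, the chance of at least one false positive is 1 − 0.95⁴ = 0.185. For correlated tests, four standard normal statistics with common correlation ρ were simulated (1 million draws per value), counting draws with at least one |z| > 1.96.

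**Step 3: four tests, success only if all are significant.** The level is then at most 5%. For power, each statistic is shifted by 0.5 / (1.48 × √(2/139)) = 2.82, that is, a true 0.5-point difference at every time. Draws with all four above 1.96 are counted.

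| Assumed ρ | Any-time rule: false-positive rate | All-four rule: power |
|---|---|---|
| 0 | 18.5% | 42% |
| 0.5 | 15.6% | 56% |
| 0.7 | 13.0% | 63% |
| 0.8 | 11.4% | 66% |
| 0.9 | 9.3% | 71% |
| 1 | 5.0% | 80% |

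A correlation that decays with distance between visits (0.7 between neighbouring times) gives 14.4% under the any-time rule, inside the same range. Counting only false positives that favour the intervention, the rate is 4.7% (ρ = 0.9) to 9.6% (ρ = 0), against a nominal 2.5%.

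**Step 4: keep four co-equal times and adjust.** Bonferroni gives 0.05 / 4 = 0.0125 per test. With 139 per group, power per time is then 62%. Restoring 80% needs 197 per group, or 394 / 0.9 = 438 randomized.

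**The case against.** The strongest reply is that no success rule is written, so no inflation has been shown. A reader might infer that the trial has four separate chances to declare success and that its false-positive risk is about three times the stated 5%. The article does not support that. It never says that one significant time is enough, and three times fits only a correlation near 0.5. The any-time figures are conditional on that rule and have to be given as a range.

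The Data analysis sentence is also looser than it first appears. Its list of times follows the pre/post comparison within arms, and the between-arm part says only that it is postoperative. The p < 0.05 statement is a general one, placed after the sentence on secondary endpoints. Four between-arm tests are therefore a reading, though the primary objective supports it directly by comparing the two care models at all four times.

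Finally, testing order, alpha allocation and the choice of joint model are ordinary content of an analysis plan, which is not shown. A pre-specified mixed-model contrast could settle the matter, and the article mentions such models. Silence on those details is no fault. But the article is not silent on timing: it positively fixes four unranked times as primary, and an analysis plan that picked one would depart from the stated primary objective.

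**Conclusion.** The point holds as a mismatch between four unranked primary comparisons with no success rule and a sample size for one comparison with no time. Under neither of the two obvious rules do the stated 5% and 80% both hold, unless the four statistics are perfectly correlated. With any-time success the error rate is about 9% to 18.5%; with all-four success power is about 71% down to 42%. Both ranges run over assumed correlations of 0.9 to 0, and the power range also assumes a true 0.5-point difference at every time.

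Two further inferences should be resisted. The 5% level is not shown to be broken, because that depends on a rule the article leaves open. Nor can it be said that 80% power is secured at 3 months, or at any other particular time, because the 0.5-point difference and SD of 1.48 are tied to none. The sample size calculation itself is correct.

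**What to change.** Before outcome data are seen, name one primary between-arm SPPB contrast, tested two-sided at 5%. Two forms would serve:

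- **One time point**, for example 3 months. The documents do not favour any particular time, so the choice is the sponsor's. The 139 per group and 310 in total then stand, provided the 0.5-point difference and SD of 1.48 hold at that time.
- **One pre-specified overall contrast** from a mixed model across the postoperative times. This needs its own power statement, because 0.5 and 1.48 describe a single comparison of two means.

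Make the remaining times secondary, or test them in a stated fixed order after the primary contrast, each at 5% and only while the preceding test is significant. Align the primary objective, Primary outcome and Data analysis sections with the choice, and say in Sample size which contrast the assumed difference and standard deviation refer to.

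The cost is wording, plus a new power calculation if the overall contrast is chosen. The downside is that a benefit seen only at a non-primary time could not be claimed as confirmatory.
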